## 4.0 TREATMENT PLAN

### 4.1 Treatment Schema

[figure not shown]

Treatment for this protocol will be administered on an outpatient basis. Each patient will receive 20mg of AT-101 orally every day for 3 weeks (21 days) of each cycle. Each treatment cycle is 28 days. Tumor tissue and blood samples will be obtained from each patient prior to beginning treatment with AT-101 (See section 9.5). Treatment of an individual patient will continue until there is objective or clinical evidence of either disease progression or treatment-related, dose-limiting toxicity, or if the patient decides to discontinue treatment for any reason. All patients will be given drug to take home and a drug calendar that explicitly details how many tablets of AT-101 the patient will be taking each day. The patient will be asked to record the amount of AT-101 actually taken as well as the date and time of each dose in a pill diary.

Prior to starting each treatment cycle the patient must meet the following criteria on Day 1 of each treatment cycle:

- $ANC \geq 1,500/\text{mcL}$
- $\text{Platelets} \geq 100,000/\text{mcL}$
- Non-hematologic toxicity recovered to  $\leq$  grade 1, tolerable grade 2 or pretherapy baseline
- No medical condition or other circumstance (including progressive disease) exists that, in the opinion of the investigator, would make the patient unsuitable for further participation in the study.

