## 5.0 DOSE MODIFICATION FOR TOXICITY

### 5.1 Dose Modification

In the event of toxicity, the dose of AT-101 will be adjusted according to the guidelines shown in the Dose Delays/Dose Modifications table that follows. Dose adjustments for hematologic toxicity are based on the blood counts obtained in preparation for the day of treatment.

Patients with adverse events that are manageable with supportive therapy may not require dose reductions (*e.g.*, nausea/vomiting may be treated with antiemetics, diarrhea may be treated with loperamide, electrolyte abnormalities may be corrected with supplements rather than by dose reduction).

| Dose Level | AT-101 Dose                                                                                                            |
|------------|------------------------------------------------------------------------------------------------------------------------|
| -2         | Only 1 dose reduction is permitted. If a patient requires more than one dose reduction they should come off treatment. |
| -1         | 10 mg, daily
(1 10-mg tablet)                                                                                       |
| 0          | 20 mg daily
(2 10-mg tablets)                                                                                       |

In the event of an adverse event at least possibly related to AT-101, the doses will be adjusted according to the guidelines shown in the Dose Modifications table that follows. If an adverse event is not covered in the table, doses may be reduced or held at the discretion of the investigator for the patient's safety.

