Patients who require dose delays will have their treatment delayed and will be re-evaluated when clinically appropriate. The re-evaluation interval will be based on standard institutional care criteria, the nature of the adverse event or toxicity observed, and the clinical judgment of the investigator. If the adverse event or toxicity is not resolved when re-evaluated, further delay may occur. If a treatment delay of more than 2 weeks (14 days) is required, the patient will be withdrawn from the treatment portion of the study, but will be followed to the resolution of the adverse event or toxicity. Treatment may also be delayed for logistic or personal reasons, but the treating investigator should contact the ABTC Central Office to discuss the case of any patient whose treatment has been delayed for more than 2 weeks (14 days) for such reasons, prior to resuming study therapy. The central office will allow up to a maximum of 4 weeks delay for personal reasons.

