|                                                                                                                                                                                                                                                                                                                                                                                                                                                                                          | Grade 3: no fever or infection       | Consider dose delays or dose reductions to the next lower dose level.                                                                                                                                                                                                                                                                                                                                                                          |
|                                                                                                                                                                                                                                                                                                                                                                                                                                                                                          | Grade 3 ANC: with fever or infection | Hold AT-101 until recovery to $ANC \geq 1.5 \times 10^9/L$ a then reduce one dose level. a                                                                                                                                                                                                                                                                                                                                          |

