|                                                                                                                                                                                                                                                                                                                                                                                                                                                                                          | Grade 4                                     | Skip dose and hold subsequent dosing until recovery to $ANC \geq 1.5 \times 10^9/L$ and platelets $\geq 100 \times 10^9/L$ then reduce one dose level. a                                                                                                                                                                                                                                                                            |
| Non-hematologic Adverse Events                                                                                                                                                                                                                                                                                                                                                                                                                                                    | Grade 0-2                                   | No dose modification; administer 100% of dose .                                                                                                                                                                                                                                                                                                                                                                                         |

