| 12-lead ECG                             | 1        |                    |                   |                    |                                                |
| Serum Biomarkers                        | 16       | 16                 |                   |                    |                                                |

- 1 – All baseline measurements must be done within 14 calendar days prior to start of treatment administration unless otherwise specified.
- 2 – See section 5.1 for guidelines for elevated serum troponin.
- 3 – Archived Tissue to be obtained and sent unstained paraffin-embedded tissue (from the most recent tumor block available).  
Investigators should make efforts to collect and ship one block or 15-20 slides. See Section 9.5 for details.
- 4 – within -3 days
- 5 – Height should be obtained at baseline
- 6 – Vital signs include temperature, blood pressure, respiratory rate, and heart rate (weight only needs to be obtained every odd cycle)
- 7 – Repeat only if > 3 calendar days since last eval/test
- 8 – If ANC < 1500 or plts < 100,000, CBCs/differentials will be repeated twice a week until counts are recovered (ANC ≥1500 or plts ≥100,000) per protocol. If counts are recovered (ANC ≥1500 or plts ≥100,000) on day of scheduled drawing do not repeat till next protocol schedule day.
- 9 – CBC with differential count and platelet count
- 10 – Na, K, HCO3, Ca, glucose, BUN, creatinine, total bilirubin, SGOT, SGPT, alkaline phosphatase, albumin, GGT, total protein
- 11 – within -5 calendar days (MRI should be obtained and evaluated prior to start of new cycle)
- 12 – Collect for at least 30 days post last dose of AT-101. Patients who are discontinued due to an AE will be followed until AE resolves.
- 13 – repeat only if > 14 days since date of last scan
- 14 – Needs to be drawn after the last dose of AT-101 in each treatment cycle
- 15 – Needs to be drawn the last day of treatment
- 16 – Serum Biomarkers are being collected within 24 hours before the first dose of AT-101 and after one week of therapy (any time during week 2 of cycle 1). See Section 9.5.2 for details.

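### Note 8 of the observations table (9.1) treats counts as recovered when either ANC or platelets recover, while 4.1 requires both; the 5.1 haematologic rows also do not refer to 4.1

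*Protocol*

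**What the plan says.** **Cycle start (Protocol 4.1).** "Prior to starting each treatment cycle the patient must meet the following criteria on Day 1 of each treatment cycle". The list that follows gives ANC of at least 1,500/mcL and platelets of at least 100,000/mcL as separate items, so both must hold.

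**Repeat counts (Protocol 9.1, note 8).** An ANC below 1,500 or platelets below 100,000 leads to twice-weekly blood counts until recovery. Recovery is defined in brackets with *or*, and the definition is repeated in the next sentence: "If counts are recovered (ANC ≥1500 or plts ≥100,000) on day of scheduled drawing do not repeat till next protocol schedule day".

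**Dose modification (Protocol 5.1).** "Dose adjustments for hematologic toxicity are based on the blood counts obtained in preparation for the day of treatment". The haematologic rows of the table then say:

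- Grade 0-2: full dose, unmodified.
- Grade 3 without fever or infection: "Consider dose delays or dose reductions to the next lower dose level". No recovery level is given.
- Grade 3 ANC with fever or infection: "Hold AT-101 until recovery to" an ANC of 1.5 x 10^9/L, then reduce.
- Grade 4: "Skip dose and hold subsequent dosing until recovery to" that ANC and platelets of 100 x 10^9/L, then reduce.

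Two limits apply: "Only 1 dose reduction is permitted. If a patient requires more than one dose reduction they should come off treatment", and "If a treatment delay of more than 2 weeks (14 days) is required, the patient will be withdrawn from the treatment portion" of the study.

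**The concern.** Note 8 sets the monitoring for a patient whose counts are too low to start a cycle. If its stopping condition is already met by the count that triggers it, the note orders no rechecks for the commonest pattern it should cover, one low count with the other normal. Sites would have no fixed schedule for finding out when that patient may restart, while the 14-day limit runs.

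The 5.1 rows raise a smaller issue. They are applied to the count that decides eligibility to start under 4.1, yet they do not cite 4.1. The grade 3 row without fever or infection offers a reduction as an alternative to a delay, and the two rows after it spell out a hold and a recovery level. A site comparing the three could conclude that no hold is needed in the first. It would then start a neutropenic patient at 10 mg, against 4.1, and use the only reduction allowed. A site that delays gives no drug until recovery and may restart at 20 mg.

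**Working it through.** There is no stated figure to reproduce. The check is a comparison of rules and thresholds.

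**1. Note 8 against 4.1.** Inputs are the two limits, 1,500/mcL and 100,000/mcL, which are the same in both places.

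- Trigger: ANC < 1,500 *or* platelets < 100,000.
- Recovered, as note 8 is written: ANC >= 1,500 *or* platelets >= 100,000.
- Eligible to start under 4.1: ANC >= 1,500 *and* platelets >= 100,000.

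| Pre-cycle counts | Trigger met | Recovered by *or* | 4.1 met |
|---|---|---|---|
| Both at or above limit | no | yes | yes |
| ANC low only | yes | yes | no |
| Platelets low only | yes | yes | no |
| Both low | yes | no | no |

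In the two middle rows the trigger and the stopping condition hold together. With illustrative values of ANC 900 and platelets 150,000, 900 < 1,500 meets the trigger, 150,000 >= 100,000 meets recovery, and 4.1 fails on ANC. When both counts are low, the literal rule stops the rechecks once the first recovers, while 4.1 still fails. The logical opposite of the trigger is the *and* form, which is the 4.1 rule.

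**2. Size in draws.** Repeat draws required by note 8 within the 14-day limit, for a patient with one count that stays low:

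- *and*: 2 per week x 2 weeks = 4.
- literal *or*: 0.

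**3. Do 4.1 and 5.1 use the same count?** Table 9.1 schedules haematology at baseline, before odd cycles, before even cycles and off treatment. On treatment, the scheduled counts are therefore the pre-cycle counts, which are also those 5.1 grades.

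**4. Grade 3 ANC against 4.1.** Appendix I puts grade 3 or 4 neutropenia at ANC < 1.0 x 10^9/L = 1,000/mcL. The shortfall from 4.1 exceeds 1,500 - 1,000 = 500/mcL, and such an ANC is under 1,000/1,500 = 67% of the floor. Every grade 3 ANC therefore fails 4.1.

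**5. Grade 0-2 row against 4.1.** By the same limit, an ANC from 1,000 to 1,499/mcL is not grade 3 or 4. It falls in the full-dose row but also fails 4.1.

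**6. What the readings would give.** Delay means 0 mg until recovery. Starting at the reduced level means 10 mg x 21 days = 210 mg, against 20 mg x 21 days = 420 mg at full dose, a 50% cut.

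**The case against.** The strongest reply on 5.1 is that the two sections are compatible. Section 4.1 is mandatory, the grade 3 row only asks the site to consider options, and a permissive option does not waive a requirement. A site that delays satisfies both. The full-dose row for grade 0-2 makes sense only if 4.1 sets timing and 5.1 sets dose. The missing recovery level also has a plain reason: the row covers all grade 3 haematologic events, including anaemia, which 4.1 does not gate, and unscheduled mid-cycle counts. All of this stands. A reader might infer that 5.1 authorises dosing a neutropenic patient. The text does not support that, because 4.1 would still have to be ignored. What remains is that 5.1 nowhere states this precedence.

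On note 8, it can be said that the note governs blood draws, not dosing; that the literal reading defeats the note's purpose; and that it refers to recovery under the protocol, which points to 4.1. Pre-cycle haematology is also due within 3 days before a cycle, so a delayed cycle cannot start without a fresh count. These points stand as limits. A reader might infer that note 8 lets a cycle start on a low ANC, or that a delayed patient would get no counts at all, and neither follows. But that a literal reading makes the note cancel itself is a reason to correct the wording. The comparison of 0 with 4 draws describes what note 8 requires, not every count a patient would have.

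**Conclusion.** Note 8 is wrong as written: its recovery test disagrees with 4.1 and, for any patient with exactly one low count, cancels the recheck it has just ordered. The size is 0 required repeat draws against about 4 over 14 days, assuming the count stays low and the *or* is followed literally.

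The 5.1 part is a missing cross-reference and a minor safety clarification, not a contradiction. It applies at cycle start, to events at least possibly related to AT-101, and to ANC. It relies on the Appendix I limit for grade 3 or 4 neutropenia, the only one printed in the protocol. The same argument for platelets would need a grade 3 platelet limit, which the protocol does not state.

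Frequency cannot be derived and is probably low: section 9.3 lists decreased neutrophils only among events whose relationship to AT-101 is undetermined. The 52-event, 56-patient design, its power and the survival analysis are not affected.

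**What to change.** - **Table 9.1, note 8:** change *or* to *and* in the two recovery clauses, so that they match 4.1. Leave *or* in the trigger.
- **Section 5.1:** add: *Whatever the grade, no cycle starts until the ANC and platelet criteria of Section 4.1 are both met; a dose reduction does not replace this delay.* This covers the grade 3 row without fever or infection and the grade 0-2 row together. The discretion in the grade 3 row stays as it is for other haematologic events and mid-cycle counts.

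The edit is two words and one sentence. In use, it adds a few blood counts for patients with one low value. It also delays an occasional patient whom a site might have started at 10 mg, and some of those delays may reach the 14-day limit and end treatment.

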#### **5.1.1 Guidelines for the Evaluation of Patients with Nausea, Vomiting, and/or Abdominal Pain**

If a patient has  $\geq$  Grade 2 nausea,  $\geq$  Grade 2 vomiting, or any abdominal pain that lasts for longer than 48 hours, AT-101 should be held and the following actions are recommended:

1. Physical examination, including the performance of vital signs
2. Screening abdominal radiography to include an abdominal series to exclude ileus, SBO, or pneumatosis intestinalis
3. Consideration for obtaining a CT scan with contrast of the abdomen should be made based on clinical judgment

If ileus, SBO, or pneumatosis intestinalis are excluded, dosing of AT-101 TMZ may be reinstated following the provisions in the above table.

If a patient is determined to have ileus, SBO, or pneumatosis intestinalis, expectant management with supportive care is recommended, unless clinical signs or symptoms are present that suggest septicemia or abdominal catastrophe that warrants surgical management.

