### **5.2 Major Events**

Major Events are non treatment-related Grade 3 and 4 hematologic and nonhematologic toxicities. Treatment should be delayed for major events if AT-101 may further complicate the non-treatment related event. If a major event requires a delay of treatment, treatment must be delayed until toxicity is resolved ( $\leq$  Grade 2 or  $\leq$  Baseline). If toxicity is not resolved in  $\leq$  2 weeks, patient will be taken off treatment. ABTC office should be consulted if you are not clear on whether to continue or delay treatment.

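### For low-grade nausea, vomiting and abdominal pain, section 5.1.1 holds AT-101 while the dose table gives full dose, and no passage says which prevails

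*Protocol*

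**What the plan says.** **Protocol 5.1.1** is a subsection of 5.1 placed directly after the dose table. Its triggers are nausea of grade 2 or more, vomiting of grade 2 or more, or "any abdominal pain that lasts for longer than 48 hours". The instruction is "AT-101 should be held and the following actions are recommended": a physical examination, abdominal films, and CT if judged necessary. If ileus, SBO and pneumatosis are excluded, "dosing of AT-101 TMZ may be reinstated following the provisions in the above table".

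**Protocol 5.1**, for adverse events at least possibly related to AT-101, says "the doses will be adjusted according to the guidelines shown in the Dose Modifications table that follows". It gives the investigator discretion to hold or reduce where an event is not in the table.

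**The dose table**, in its non-hematologic rows, has three tiers:
- Grade 0-2: "No dose modification; administer 100% of dose".
- Grade 2, persistent and intolerable: consider a delay or a one-level reduction.
- Grade 3 or 4: hold until recovery, then reduce one level if continued therapy is warranted.

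The table has a separate row for elevated troponin, with its own hold-and-evaluate instruction. It has no row or cross-reference for the events in 5.1.1.

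**The concern.** The same patient with the same symptom gets opposite instructions depending on which passage the site opens. The difference falls where 5.1.1 has its purpose: whether drug continues before ileus or obstruction has been excluded.

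The protocol's background treats bowel obstruction and ileus as an important toxicity of this agent. As of November 2006 it reports 24 patients with events that were, or may have been, obstruction or ileus. The regimens involved were continuous daily dosing or 21 of 28 days, and the latter is the schedule used here.

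A hold also has consequences. Under sections 5.1 and 10.0, a toxicity delay beyond 14 days takes the patient off treatment. Different readings could therefore affect how long a patient stays on drug.

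**Working it through.** No sample size, power or error rate is involved, so there is nothing to calculate. The check sets the two rules side by side for the same event, assumed at least possibly related to AT-101 so that the table applies.

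| Event | Section 5.1.1 | Dose table | Conflict? |
|---|---|---|---|
| Grade 2 nausea or vomiting beyond 48 h, tolerable | Hold and evaluate | Full dose | Yes |
| The same, persistent and intolerable | Hold and evaluate | Consider delay or reduction | Yes: directed against optional |
| Grade 1 abdominal pain beyond 48 h | Hold and evaluate | Full dose | Yes |
| Grade 2 abdominal pain beyond 48 h | Hold and evaluate | Full dose, or consider delay or reduction if persistent and intolerable | Yes |
| Grade 3-4 nausea or vomiting | Hold and evaluate | Hold, then reduce if therapy continues | No conflict on the hold |

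**The 48-hour phrase.** The sentence does not make clear whether 48 hours qualifies all three symptoms or only the pain. The table above uses symptoms beyond 48 hours, so the conflict stands on either reading.

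**Is precedence stated anywhere?** No. Section 5.1 sends related events to the table, and its discretion clause reaches only events that the table does not cover. Low-grade nausea, vomiting and pain fall in the grade 0-2 row. The troponin row shows that the authors put one event-specific exception into the table; they did not do so for these events. The remark in 5.1 that nausea and vomiting may be managed with antiemetics concerns dose reductions, so it does not decide whether to hold.

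**The restart sentence.** It names TMZ beside AT-101. Section 11.4 describes a single-agent trial and section 4.1 gives AT-101 alone, so no second drug exists to restart.

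**Minor related point: section 5.2 against section 4.1.** For unrelated grade 3-4 events, 5.2 says "treatment must be delayed until toxicity is resolved" and sets that at grade 2 or lower, or baseline. Section 4.1 says "Prior to starting each treatment cycle the patient must meet the following criteria on Day 1 of each treatment cycle", and makes no exception by cause. It asks for ANC of at least 1,500/mcL, platelets of at least 100,000/mcL, and non-hematologic recovery to grade 1, to a grade 2 the patient tolerates, or to the level before therapy. The Appendix I worksheet places grade 3-4 neutropenia at ANC below 1.0 x 10^9/L, which is 1,000/mcL. An ANC from 1,000 to below 1,500 therefore ends the delay under 5.2 but does not permit a cycle start under 4.1. A non-tolerable grade 2 event above baseline behaves the same way. Both cases arise only on Day 1 of a cycle.

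**The case against.** The best defence is that 5.1.1 is a specific rule following a general one. It is headed with the exact symptoms and reads as a sequence: pause, examine, then return to the table for dosing. On that view the cross-reference links the two passages, and the troponin row shows that hold-and-evaluate rules beside general grade rows are the protocol's normal pattern. The reading is plausible and many sites would adopt it. But it is not stated. The troponin exception sits inside the table, where a site reading the table will see it; the 5.1.1 exception does not.

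Four stronger readings are tempting, and the documents do not support them:

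- **That 5.2 and 4.1 contradict each other.** Section 5.2 sets a minimum for ending a delay; 4.1 is a gate on Day 1. Both can be applied together, and 5.2 tells sites to consult the ABTC office if unsure. What remains is that 5.2 calls an event resolved at a level 4.1 may not accept.
- **That 24 of 32 serious events were obstruction or ileus.** The background reports 32 SAEs and, separately, 24 patients. It does not say that the second group lies within the first. It adds that several events were considered unrelated and that they tended to occur at higher doses. It also reports that the daily single-agent dose was later reduced to 20 mg, the dose used here.
- **That the conflict must arise often** because nausea, vomiting and abdominal pain are each listed at more than 20%. That list gives neither grade nor duration, so it cannot show how often the triggers in 5.1.1 are met.
- **That exposure and toxicity rates will differ between sites.** This is possible, but nothing in the protocol allows its size to be estimated.

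**Conclusion.** The contradiction between 5.1.1 and the dose table holds on the text. It is limited to related grade 2 nausea or vomiting and related grade 1-2 abdominal pain lasting more than 48 hours. It rests on one assumption: that a reader may not treat 5.1.1 as overriding the table when the protocol never says so. How often it would matter cannot be derived from the documents.

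It is worth correcting despite the unknown frequency, because it concerns continuing drug before a recognised serious toxicity has been excluded. TMZ in the restart sentence is a plain error. The relation of 5.2 to 4.1 is a minor clarification.

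**What to change.** - Reconcile 5.1.1 with the dose table: state in the table, as is done for troponin, which passage governs nausea, vomiting and abdominal pain that meet the 5.1.1 triggers. The clinical content is for the sponsor to decide.
- Delete TMZ from the restart sentence in 5.1.1.
- Add to 5.2 a cross-reference to the Day 1 criteria in 4.1, making clear how the two apply together.

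The cost is a few lines of wording in the table, 5.1.1 and 5.2. The sample size and the statistical analysis do not change.
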